# Extracorporeal carbon dioxide removal for treatment of exacerbated chronic obstructive pulmonary disease (ORION): study protocol for a randomised controlled trial

**DOI:** 10.1186/s13063-021-05692-w

**Published:** 2021-10-19

**Keywords:** Acute exacerbations of chronic obstructive pulmonary disease, COPD, Extracorporeal CO2 removal, ECCO2R, Non-invasive ventilation, NIV

## Abstract

**Background:**

Hypercapnic exacerbations are severe complications of chronic obstructive pulmonary disease (COPD), characterized by negative impact on prognosis, quality of life and healthcare costs. The present standard of care for acute exacerbations of COPD is non-invasive ventilation; when it fails, the use of invasive mechanical ventilation is inevitable, but is associated with extremely poor prognosis. Extracorporeal circuits designed to remove CO_2_ (ECCO_2_R) may enhance the efficacy of NIV to remove CO_2_ and avoid the worsening of respiratory acidosis, which inevitably leads to failure of non-invasive ventilation. Although the use of ECCO_2_R for acute exacerbations of COPD is steadily increasing, solid evidence on its efficacy and safety is scarce, thus the need for a randomized controlled trial.

**Methods:**

multicenter randomized controlled unblinded clinical trial including 284 (142 per arm) patients with acute hypercapnic respiratory failure caused by exacerbation of COPD, requiring respiratory support with NIV. The primary outcome is event free survival at 28 days, a composite outcome defined by survival in absence of prolonged mechanical ventilation, severe hypoxemia, septic shock and second episode of COPD exacerbation. Secondary outcomes are incidence of endotracheal intubation and tracheostomy, intensive care and hospital length-of-stay and 90-day mortality.

**Discussion:**

Acute exacerbations of COPD represent a significant burden in terms of prognosis, quality of life and healthcare costs. Lack definite evidence despite increasing use of ECCO_2_R justifies a randomized trial to evaluate whether patients with acute hypercapnic acidosis not responsive to NIV should undergo invasive mechanical ventilation (with all serious related risks) or be treated with ECCO_2_R to avoid invasive ventilation but be exposed to possible adverse events of ECCO_2_R. Owing to its pragmatic nature, sample size and composite primary outcome, this trial aims at providing valuable answers to relevant questions for clinical treatment of acute exacerbations of COPD.

**Trial registration:**

ClinicalTrials.gov, NCT04582799. Registered 12 October 2020, .

**Supplementary Information:**

The online version contains supplementary material available at 10.1186/s13063-021-05692-w.

## Background

Chronic obstructive pulmonary disease (COPD) is the third leading cause of death worldwide, resulting in a social and economic burden that is substantial and increasing [1, 2]. Hypercapnic exacerbations affect the prognosis (hospital mortality is approximately 10%) and quality of life (long-term outcome is poor) of patients with COPD [3, 4]. In addition, hypercapnic exacerbations of COPD have serious negative impacts on healthcare costs. Thus, prompt treatment of exacerbations may impact the clinical progression of COPD by ameliorating quality of life and prognosis [5, 6].

The pathophysiological hallmarks of COPD patients include expiratory flow limitation and small airway closure [7], making a prolonged expiratory time the only compensatory mechanism to maintain a stable tidal breathing. COPD exacerbations result in higher respiratory rates and reduced expiratory time, with decreased capacity of the respiratory muscles to generate pressure [7–9]. The consequent reduction of alveolar ventilation leads to a further worsening of CO_2_ retention and increased work of breathing [7].

The standard of care for patients with hypercapnic COPD exacerbations in the ICU is non-invasive ventilation (NIV) [10]. When NIV fails (i.e., arterial pH remains < 7.30), invasive ventilation through endotracheal intubation is initiated to restore adequate gas exchange. Patients requiring invasive mechanical ventilation have greater odds of death compared with patients successfully treated with NIV alone [4, 11].

Extracorporeal circuits designed to remove CO_2_ (ECCO_2_R) may add to improved efficacy of NIV by removing CO_2_ [12–15] and avoid worsening of respiratory acidosis [16–18]. Although available studies are limited to case series [12], several ECCO_2_R devices have been developed and proposed for the clinical use in patients with COPD [19]. These systems often represent modifications of renal replacement therapy circuits and are characterized by: (a) veno-venous by-pass systems; (b) extracorporeal blood flow of 0.3-0.5 liters/min; (c) 13 Fr bore catheters or a single co-axial catheter; (d) very low heparin doses or no heparin; (e) minimal volumes for circuit priming; (f) artificial membrane lung connected to a source of 100% O_2_ (usual flow 6-8 liters/min). These systems are able to reduce PaCO_2_ by 20-25% [20, 21]. These circuits have evolved in time and may be efficient even when using relatively small-bore catheters and low blood flows [19]. These modifications may reduce the side effects that have complicated earlier studies and underscore the rationale to perform this study.

### Trial hypothesis and main objective

A recent matched cohort study [14] with historical control, compared “*NIV-plus- ECCO*_*2*_*R*” and “*NIV-only*” in patients at risk of NIV failure, and showed that (a) the hazard of being intubated was three times higher in patients treated with “*NIV-only*” than in patients treated with “NIV-*plus*- *ECCO*_*2*_*R*”; (b) hospital mortality was significantly lower in “NIV *plus* ECCO_2_R” than in “NIV-*only*” [8% (95% CI 1.0-26.0%) vs. 33% (95% CI 18.0-57.5%), respectively]. However, ECCO_2_R-related complications were observed in almost half of the patients. A recent systematic review [12] evaluated the efficacy and safety of ECCO_2_R in patients with hypercapnic respiratory failure across 12 studies and showed that the majority of patients were either successfully weaned from mechanical ventilation or sustained on NIV, avoiding intubation. However, this high success rate was associated with a high frequency of potentially severe complications [12].

Accordingly, the main objective of this randomized multicenter clinical trial is to test the hypothesis that in patients with acute life-threatening exacerbation of COPD, use of ECCO_2_R could increase event-free survival as compared to standard of care. Event free survival is defined as survival at day 28 free of septic shock, second episode of COPD exacerbation, occurrence of severe hypoxemia, and prolonged mechanical ventilation.

## METHODS/DESIGN

### Trial design

This trial is a multicenter, prospective, randomized, controlled, unblinded clinical trial. The framework of the trial is superiority. The trial will include 284 patients with acute hypercapnic respiratory failure caused by exacerbation of COPD.

### Inclusion criteria

Patients older than 18 and younger than 90 yearsDocumented clinical history of COPDICU admission for exacerbation of COPD requiring NIV support

After two hours of NIV at least two of the following criteria for high risk of NIV-failure [14, 22] must be fulfilled:
arterial pH ≤ 7.25respiratory rate ≥30 breaths/minuse of accessory muscles or paradoxical abdominal movements

### Exclusion criteria

mean arterial pressure <60 mmHg despite infusion of fluids and vasoactive drugsratio of arterial-to-inspired oxygen O_2_ fraction (PaO_2_/FiO_2_) ≤ 150 with FiO_2_ of less than 0.6 and PEEP of at least 5 cm H_2_Ocontraindications to anticoagulation (i.e. any of the following: platelet count <50,000/mm^3^; international normalized ratio (INR) >1.5; stroke or severe head trauma or intracranial arterio-venous malformation, or cerebral aneurysm, or central nervous system mass lesion within the previous 3 months; epidural catheter in place or expected to be positioned during the study; history of congenital bleeding diathesis; gastrointestinal bleeding within the 6 weeks prior to study entry; esophageal varices, chronic jaundice, cirrhosis, or chronic ascites; trauma);heparin-induced thrombocytopeniabody weight >120 kgcontraindication to continuation of active treatmentfailure to obtain consentdifficult or impossible catheterization of femoral and jugular veinpneumothoraxsevere liver insufficiency (Child-Pugh scores >7) or fulminant hepatic failurediagnosis of acute or chronic neuromuscular diseasechronic mechanical ventilation prior to hospital admissionmoribund patientinclusion in other interventional trials

### Primary outcome

The primary outcome is event free survival, defined as survival at day 28 free of any of the following: (a) prolonged mechanical ventilation; (b) development of septic shock; (c) occurrence of severe hypoxemia; (d) occurrence of a second episode of COPD exacerbation (either or not requiring mechanical ventilation); (e) 28-day all cause death. By analyzing the relevant epidemiological literature on COPD exacerbations [23–33] and on their complications [34–37] we could determine that these five elements are the most common complications in hospitalized AECOPD patients.
**Prolonged mechanical ventilation** is defined as mechanical ventilation (invasive and non-invasive) applied for ≥ 14 days uninterrupted for more than 48 hours.**Septic shock** is defined by the presence of (a) sepsis (organ dysfunction caused by proven infection with an increase in the Sequential Organ Failure Assessment (SOFA) score of 2 points or more); (b) need for vasopressors to maintain a mean arterial pressure of 65 mmHg or greater; (c) serum lactate levels greater than 2 mmol/l (>18mg/dl) in the absence of hypovolemia.**Severe hypoxemia** is defined as occurrence of a ratio of arterial-to-inspired oxygen O_2_ fraction (PaO_2_/FiO_2_) ≤ 150 with FiO_2_ of less than 0.6 and PEEP of at least 5 cm H_2_O for at least 12 hours.**Second episode of COPD exacerbation** is defined as occurrence of sustained (≥24 h) increase in cough, sputum production, dyspnea and arterial pH≤7.30 (either or not requiring mechanical ventilation).**28-day all-cause mortality** is defined at 672 hours from randomization. All patients will be classified as either “alive at Study Day 28” or, if dead, “dead at Study Day 28.” For example, day zero is the day of randomization and day 1 is the next day and encompasses all events that occur midnight-to-midnight, etc.

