minute ventilation <15 l/min;PaO_2_/FiO_2_ ratio > 150 to 200; with PEEP ≤ 5 cmH_2_OFiO_2_ ≤ 0.4;pH > 7.30rapid shallow breathing index < 105 [42]

Pressure support ventilation (PSV) will be used to gradually decrease mechanical ventilatory support. Patient will be defined as “weaned from mechanical ventilation” (invasive or non-invasive) if the following 4 criteria are met for the last 30 minutes during a spontaneous breathing trial (SBT):
SpO_2_≥90% and/or PaO_2_≥60 mmHg (PaO_2_ to take precedence if both available)Respiratory rate ≤30 bpmpH ≥ 7.35No respiratory distress (defined as 2 or more of the following):
Heart rate ≥ 120% of the 6:00 a.m. rate for ≥5 minutesSignificant use of accessory musclesAbdominal paradoxDiaphoresisMarked dyspnea as subjectively assessed by the investigator

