Interruptions of ECCO_2_R (for any cause) lasting longer than 6 hours are to be considered ‘treatment failure’ and lead to termination of the experimental protocol.

All concomitant therapies foreseen by the standard of care of enrolled patients are allowed.

Post-trial care will be delivered according to the standard of care for AECOPD patients.

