#### Evaluation of the primary endpoint

EFS will be estimated using the Kaplan-Meier estimator applied to the ITT population, and compared between those who received NIV plus ECCO2R and those who did receive only NIV using the stratified log-rank test.

In addition, the Hazard Ratio (HR), along with 95% confidence intervals, will be estimated from a stratified Cox model with treatment group as a covariate.

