#### Evaluation of secondary endpoints

All components of the primary composite endpoint (singleton) will be examinated separately as independent proportion. The cumulative incidence of sepsis, hypercapnic respiratory failure, hypoxemic respiratory failure, prolonged mechanical ventilation >28days, tracheostomy and endotracheal intubation will be estimated with the Gooley method, to take into account the competitive risk of death, and compared with the Grey test. The Fine and Grey model will be used to estimate adjusted HR and their 95% CI. In addition, overall survival (OS) will be analyzed with Kaplan-Meier method and compared with the log rank test. A Cox proportional hazard model (if appropriate) will be used to estimate the Hazard Ratios (HR) and the 95% CI.Hospital length of stay and ICU length of stay will be described in each arm as median and interquartile range; they will be compared with the Wilcoxon rank sum test. The 95% confidence interval (CI) of the mean difference of measure will be estimated with a bootstrap method.Hospital mortality will be expressed as rate and a Chi square test will be used to evaluate the difference between the two groups.Incidence of adverse events and severe adverse events will be expressed as rate and a Chi square test will be used to evaluate the difference between the two groups.

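### The prolonged-ventilation component has an ambiguous 48-hour rule, no daily minimum and no link to the protocol's own weaning criteria, so intermittent NIV after weaning may or may not be a primary event

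*Protocol article*

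**What the plan says.** All places are in the protocol article.

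- **Primary outcome.** The section states: "The primary outcome is event free survival, defined as survival at day 28 free of any of the following". Five components follow, including all-cause death. Prolonged mechanical ventilation "is defined as mechanical ventilation (invasive and non-invasive) applied for ≥ 14 days uninterrupted for more than 48 hours". No minimum number of hours per day is given.
- **Inclusion and exclusion criteria.** Every patient has had two hours of NIV before qualifying. Patients on chronic ventilation before admission are excluded. Nothing is said about long-term NIV started later.
- **Group A: Standard of care.** "Patient will be defined as “weaned from mechanical ventilation” (invasive or non-invasive) if the following 4 criteria are met" during a spontaneous breathing trial. The Group B section adopts the same criteria. The definition of prolonged ventilation does not refer to them.
- **End of the Group B section.** "All concomitant therapies foreseen by the standard of care of enrolled patients are allowed". Nocturnal and home NIV are named nowhere.
- **Evaluation of the primary endpoint.** "EFS will be estimated using the Kaplan-Meier estimator applied to the ITT population", with a stratified log-rank test and a stratified Cox model. No component is weighted or ranked.
- **Evaluation of secondary endpoints.** "All components of the primary composite endpoint (singleton) will be examinated separately as independent proportion". The list of cumulative incidences that follows contains "prolonged mechanical ventilation >28days".

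**The concern.** The protocol defines when a patient is off ventilation, then leaves that definition out of the one primary component that measures time on ventilation. Combined with a 48-hour phrase that can be read two ways and no daily minimum, this means two sites could classify the same patient differently.

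The patient at issue has met the weaning criteria and goes on using NIV for part of each day, for example at night. Depending on the reading, that patient is either event-free or has a primary event, and in the log-rank test such an event counts as much as a death. The trial is unblinded, and whether to continue intermittent NIV after weaning is a decision of the treating team. A choice made with knowledge of the arm could therefore create or avoid primary events.

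**Working it through.** **1. The two readings.**

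- Reading 1: the run lasts at least 14 days and no interruption exceeds 48 hours.
- Reading 2: ventilation must itself be continuous for more than 48 hours to count.

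Reading 1 is the more sensible. Beside a 14-day minimum, an allowance for breaks is the only useful work a 48-hour figure can do, whereas continuity for more than 48 hours adds nothing to 14 uninterrupted days.

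**2. Which patterns qualify** (assumption: 8 hours per NIV night; 14 days = 336 hours).

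| Pattern | Gap | Hours ventilated in 14 days | Reading 1 | Reading 2 |
|---|---|---|---|---|
| Every night | 24 − 8 = 16 h | 14 × 8 = 112 (33%) | counts | does not |
| Alternate nights | 48 − 8 = 40 h | 7 × 8 = 56 (17%) | counts | does not |
| Every third night | 72 − 8 = 64 h | – | does not | does not |

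**3. Timing.** The run must reach 14 days by day 28. All patients are on NIV at entry, so a run never broken for more than 48 hours completes at about day 14. After a longer break, a new run must start by about day 28 − 14 = 14.

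**4. The plan's effect size.** Sample size gives 40% event-free in the control group, a hazard ratio of 0.67 and a target of 54%. Check: 0.40^0.67 = 0.541, ln 0.54 / ln 0.40 = 0.672 and 0.54 / 0.40 = 1.35. These figures agree with each other.

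**5. Equal relabelling in both arms.** The documents give no frequency. Let q be the share of otherwise event-free patients who become events. The event-free proportions are then 0.40(1 − q) and 0.54(1 − q), and under proportional hazards HR = ln S_B / ln S_A.

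| q (assumed) | Control | ECCO2R | Difference | HR |
|---|---|---|---|---|
| 0 | 40.0% | 54.0% | 14.0 points | 0.67 |
| 10% | 36.0% | 48.6% | 12.6 points | ln 0.486 / ln 0.36 = 0.71 |
| 20% | 32.0% | 43.2% | 11.2 points | ln 0.432 / ln 0.32 = 0.74 |
| 30% | 28.0% | 37.8% | 9.8 points | ln 0.378 / ln 0.28 = 0.76 |

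These events would fall at about day 14 or later, so the hazard ratios are only a convenient summary.

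**6. Unequal relabelling, as an illustration.** With q = 10% in the ECCO2R arm only, 40.0% vs 48.6% gives ln 0.486 / ln 0.40 = 0.79. With q = 10% in the control arm only, 36.0% vs 54.0% gives ln 0.54 / ln 0.36 = 0.60. The estimate can move either way from 0.67.

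**7. The second threshold.** The primary definition uses 14 days or more, and the secondary-endpoint text uses more than 28. A run counted from randomisation cannot exceed 28 days within a 28-day window, so the two statements cannot describe the same component.

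**The case against.** Several points on the other side are fair.

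- **Counting NIV is evidently deliberate,** and a count of ventilated days is more objective than a judgement about why NIV is used. This stands, and it rules out a remedy based on labelling NIV acute or elective. The weaning criteria also include one subjective item (marked dyspnoea), and in Group B weaning from ECCO2R must come first, so tying the component to weaning has a cost.
- **The article condenses a full protocol,** which may hold the missing link. That is possible, but the article states the primary definition in full and its wording is ambiguous as it stands.
- **The 60% control event rate already includes prolonged ventilation.** If its sources counted patients on intermittent NIV, subtracting q counts some of them twice. This cannot be checked from the documents. Under equal q the relative gain also stays at 1.35 (for example 48.6 / 36.0), so the loss is in the absolute difference and the hazard ratio.
- **Equal weight with death is a feature of any time-to-first-event composite,** and the components are also examined singly. That would show the problem but would not correct the primary test.

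A reader might infer more: that any weaned patient put on permitted nocturnal or home NIV becomes a failure, and that this necessarily dilutes the effect. The documents do not support either inference. The first rests on one reading of the 48-hour phrase, on a general permission that does not name such NIV, and on a run reaching 14 days by day 28. The second follows only from equal q. Patients extubated to intermittent NIV are reached too, and if intubation is commoner in the control arm, as the trial's rationale implies, events could be added there.

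**Conclusion.** The definition needs repair. As written, whether a patient who has met the protocol's weaning criteria but continues intermittent NIV has a primary event depends on how an unclear phrase is read, and on the more sensible reading the answer can be yes. This follows from the text alone.

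The size does not follow from the text. With an assumed equal share of 10 to 30%, the planned difference of 14 points falls to between 12.6 and 9.8 points and the hazard ratio moves from 0.67 to between 0.71 and 0.76. With unequal use between arms, the direction of bias is not fixed. The conflict between the 14-day and 28-day thresholds holds whatever q is.

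**What to change.** 1. Under Primary outcome, state the 48-hour rule in words that allow one reading only.
2. End the ventilation episode at the documented time the weaning criteria are met, the same way in both arms. Add an objective rule, based on recorded ventilation times, for when later ventilation reopens the episode. Do not rely on an investigator's label of acute or elective.
3. Record post-weaning intermittent NIV in the eCRF in both arms.
4. Prespecify a sensitivity analysis of the primary outcome that counts this NIV the other way.
5. Reconcile the 14-day definition with the 28-day one under Evaluation of secondary endpoints.

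These changes affect how events are counted, not how patients are treated. The cost is somewhat fewer prolonged-ventilation events, one extra eCRF field, and reliance on breathing-trial records that include one subjective item. Trial status says recruitment had not begun, so the change is cheap now and would be hard to defend once unblinded data have accrued.

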### Secondary outcomes

Secondary outcomes are the following:
Cumulative incidence of endotracheal intubationCumulative incidence of tracheostomyHospital length-of-stayICU length-of-stay90-day mortalityIncidence of adverse events as defined in the ‘Safety’ paragraph (see below)

### Trial procedures

#### Informed consent

Informed consent will be taken by trained investigators. Before enrollment every patient must sign a written consent form for trial participation and for personal data processing. Anytime the patient is incapacitated and/or unable to fully understand the information provided, consent may be delayed (i.e., obtained after enrollment, as soon as the patient is again able to understand the information provided).

##### Randomization

Central randomization by blocks stratified only by center. The randomization is centralized: a random sequence stratified by center will be generated in order to guarantee a balancing of the arms within the center; the sequence will be implemented following a block algorithm. The random sequence will be generated by a server run by the coordinating center. Participant sites will obtain the allocation of each enrolled patient upon enrolment, after checking for inclusion/exclusion criteria.

##### Data collection

For eligible patients, study data will be collected after enrollment (Fig. 1). Study data will be collected and managed using REDCap electronic data capture tools hosted on a secure server at University of Bologna [38, 39]. Access to the study eCRF will be provided to all participating sites. All participant data will be stored anonymously through the use of codes. Participants’ identification data will be saved on an external memory, accessible only to study coordinators.

